### Interventions

**Group 1 (Control): Topical Clobetasol Propionate 0.05% Ointment.** Patients in this group will receive topical Clobetasol Propionate 0.05% ointment as their treatment modality for hand eczema. They will be instructed to apply the ointment twice daily over the affected areas. The treatment duration will extend for 4 weeks.

**Group 2 (Experimental): Topical Tofacitinib 2% Ointment.** Patients in this group will receive topical Tofacitinib 2% ointment as their treatment modality for hand eczema. Similar to Group 1, they will be instructed to apply the ointment twice daily over the affected areas. The treatment duration will also be 4 weeks.

**Application instructions:** Patients in both groups will be educated on properly applying the assigned ointments. They will be instructed to wash their hands before applying a thin layer of the ointment evenly on the affected areas, avoiding contact with eyes and mucous membranes. Patients will be advised not to bandage or cover the treated areas unless directed by the investigator. Additionally, they will be instructed to avoid excessive sun exposure and use sunscreen on treated areas.

**Follow-up visits:** Participants from both groups will be scheduled for followup visits at 2 weeks and 4 weeks after the initiation of treatment. During these visits, clinical photographs will be taken with the patient’s informed consent, and the Hand Eczema Severity Index (HECSI)
^
5
^ score will be recorded to assess the efficacy and side effects of the respective interventions.

**Monitoring:** The study will be monitored to ensure adherence to the assigned interventions, proper data collection, and participant safety. Adverse events, if any, will be documented and reported. Regular communication with participants will be maintained to address any concerns or queries they may have during the study.

**Adjustments:** Any deviations from the study protocol will be documented, and appropriate measures will be taken to address them. Adjustments will be made in consultation with the Institutional Ethics Committee if necessary.

**Blinding:** The study will be single-blinded, with the participants unaware of their assigned treatment group. This helps minimize bias in reporting outcomes.

**Code break:** In a medical emergency or if unblinding becomes necessary for clinical management, a code break procedure will be in place, ensuring that the treating physician can access information about the assigned intervention while keeping the participant blinded.

**Adherence monitoring:** Participants will be asked to return unused medication at each followup visit to assess adherence. Additionally, self-reported adherence will be recorded during followup assessments. These interventions and allocation procedures aim to systematically evaluate the comparative efficacy and side effects of topical Clobetasol Propionate 0.05% ointment and topical Tofacitinib 2% ointment in managing hand eczema.

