**Methods:**

The study will be a single-blinded, parallel-group, randomized controlled trial conducted at the Dermatology outpatient department of Acharya Vinoba Bhave Rural Hospital Sawangi Meghe, Wardha, from March 2023 to September 2025. Eligible participants diagnosed with hand eczema will be randomized into two groups: Group 1 will receive Clobetasol Propionate 0.05% ointment, and Group 2 will receive Tofacitinib 2% ointment. The primary outcome measure is the change from baseline in the Hand Eczema Severity Index (HECSI) score, assessed at two weeks and four weeks. Statistical analysis will utilize appropriate parametric and non-parametric tests, with a p-value <0.05 considered significant.

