**Expected Outcome:**

The study is anticipated to provide insights into the comparative efficacy and safety of Tofacitinib and Clobetasol Propionate in managing hand eczema. A favorable outcome for Tofacitinib could suggest its potential as an alternative or adjunctive therapy, offering a more targeted approach with fewer side effects. The findings may contribute to optimized treatment strategies for hand eczema, improving patient outcomes and guiding future research in dermatological therapeutics.

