### Objectives

1.To evaluate the efficacy of topical tofacitinib 2% ointment in hand eczema.2.To evaluate the efficacy of topically applied clobetasol propionate 0.05% ointment for hand eczema.3.To compare the effect of topically applied tofacitinib 2% ointment and topically applied clobetasol propionate 0.05% ointment in hand eczema.4.To study the side effects of topical clobetasol propionate 0.05% ointment and topical Tofacitinib 2% ointment.

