**Data collection:** Data collection will include clinical assessments, HECSI score recording, and the capture of clinical photographs during each followup visit.10.
**Adverse event reporting:** Participants will be encouraged to report any adverse events or concerns during the study. Adverse events will be documented, assessed for severity, and reported to the Institutional Ethics Committee as per regulatory requirements.11.
**End of study:** The study will conclude in September 2025, and participants will be thanked for participating. Final data analysis and interpretation will be conducted, and the study findings will be disseminated through publications and presentations.

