## Discussion

Hand eczema is a prevalent dermatological condition that substantially burdens affected individuals, impacting their daily lives and often requiring long-term management.
^
6
^ The choice of topical corticosteroids, such as Clobetasol Propionate, is a conventional approach, but concerns about prolonged use and potential side effects necessitate exploring alternative therapeutic options.
^
7
^ This study protocol outlines the design of a randomized controlled trial comparing the efficacy of topical Tofacitinib 2% ointment with topical Clobetasol Propionate 0.05% ointment in managing hand eczema.

The rationale for exploring Tofacitinib lies in its mechanism of action as a Janus kinase (JAK) inhibitor, which modulates intracellular signaling pathways involved in the inflammatory response.
^
8
^ While Tofacitinib has shown promise in conditions like psoriasis,
^
9
^ its efficacy and safety in hand eczema remain to be elucidated. The comparison with Clobetasol Propionate, a well-established treatment, will provide valuable insights into the potential advantages of Tofacitinib in terms of efficacy and side effect profiles.

The study’s methodology, including the use of a single-blinded randomized controlled trial design, rigorous inclusion and exclusion criteria, and standardized outcome measures, enhances the internal validity of the findings. Including a placebo group could have provided additional insights, but ethical considerations and the necessity of active treatment for hand eczema guided the decision to compare two active treatments.

The choice of the Hand Eczema Severity Index (HECSI) score as the primary outcome measure aligns with its established use in assessing the severity of hand eczema.
^
5
^ This comprehensive scoring system considers multiple clinical signs and provides a quantifiable measure for evaluating treatment efficacy.

One potential limitation of this study is its hospital-based nature, which may limit the generalizability of the findings to the broader population. Additionally, the study’s relatively short duration may not capture long-term effects or relapse patterns. However, the study’s strengths, including the robust study design, systematic randomization, and rigorous statistical analyses, contribute to its credibility and potential impact on clinical practice.

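### HECSI, an eczema severity score, is given the task of assessing side effects, and the only other stated way of eliciting them is participant reporting, so capture may be incomplete or uneven between arms

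*Protocol article*

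**What the plan says.** All references are to the protocol article.

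- **Interventions, follow-up visits.** At 2 and 4 weeks photographs are taken and the HECSI "score will be recorded to assess the efficacy and side effects of the respective interventions".
- **Abstract, Methods.** "The primary outcome measure is the change from baseline in the Hand Eczema Severity Index (HECSI) score, assessed at two weeks and four weeks".
- **Discussion.** Choosing HECSI as the primary outcome "aligns with its established use in assessing the severity of hand eczema", and the score "considers multiple clinical signs and provides a quantifiable measure for evaluating treatment efficacy". Side effects are not mentioned there as something it measures.
- **Objectives, item 4.** "To study the side effects of topical clobetasol propionate 0.05% ointment and topical Tofacitinib 2% ointment".
- **Enrollment, adverse event reporting.** "Participants will be encouraged to report any adverse events or concerns during the study". Events are then documented, assessed for severity and sent to the ethics committee.
- **Enrollment, data collection.** Each follow-up visit includes clinical assessments, HECSI and photographs, listed as three items. What the clinical assessments cover is not said.
- **Interventions, blinding.** The trial is single-blinded, and the participants are the blinded party.
- **Statistical analysis.** Adverse event incidence is compared between arms with a chi-square or Fisher's exact test.

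**The concern.** One score is asked to measure both benefit and harm, although the article's own description of it supports only benefit. HECSI also carries the primary efficacy comparison, so a HECSI value cannot by itself show whether a change on the hands is disease or a reaction to the ointment.

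If HECSI is set aside as a side-effect instrument, the stated means of finding side effects is what participants choose to report. Volunteered reports can miss signs that a patient does not notice or does not think worth mentioning. They also depend on how staff prompt and record, and staff are not stated to be masked.

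Side effects are a named objective and have a planned between-arm test. Concern about corticosteroid side effects is also part of the article's reason for running the trial. If events are under-recorded, or recorded more readily in one arm, the comparison of incidence can mislead in either direction.

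**Working it through.** The article states no figure for side effects, so there is none to reproduce. The 36 per group in the Sample size section comes from efficacy proportions and does not bear on how side effects are measured. The check compares the stated passages.

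**Step 1: is HECSI described anywhere as a side-effect measure?** Only the follow-up sentence gives it that role. The Discussion describes it by eczema severity and efficacy, and the abstract and the Statistical analysis section use it for efficacy. The follow-up sentence is at odds with the rest of the article.

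**Step 2: what other sources of side-effect data are stated?**

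| Source | Where | Tied to side effects? | Same for every patient? |
|---|---|---|---|
| Participant reports | Enrollment, adverse event reporting | Yes | No, it depends on what is volunteered |
| Documentation and severity assessment | Interventions, monitoring; Enrollment | Yes | It applies to events already found |
| Clinical assessments at each visit | Enrollment, data collection | Not stated | Content not stated |
| Photographs at follow-up | Interventions; Enrollment | Possibly, as they share the HECSI sentence | Yes, given consent, but a reading for reactions is not described |

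So participant reporting is the only elicitation route, apart from HECSI, that the article links explicitly to side effects.

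**Step 3: what does this do to the planned comparison?** Let p1 and p2 be the true proportions of patients with a local reaction in the two arms, and c1 and c2 the proportions of those patients in whom it is recorded, assuming no false records. The expected observed difference is

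c2·p2 − c1·p1.

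- With equal capture (c1 = c2 = c) it becomes c·(p2 − p1). For c below 1, a true difference shrinks towards zero.
- With equal true risk (p1 = p2 = p) and unequal capture it becomes (c2 − c1)·p, which is a difference produced by recording alone.

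The article gives none of p1, p2, c1 or c2. The direction of each problem is clear, but its size cannot be calculated.

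**Step 4: is unequal capture possible under this design?** Participants are blinded, which helps keep their own reports even. Nobody who asks, examines or records is stated to be blinded, and no uniform question is described. Unequal capture is possible; the article does not show that it will occur.

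**The case against.** The strongest reply is that this is a loose sentence and the safety plan behind it is adequate. Adverse events are documented, assessed for severity and compared between arms, and nothing says that the incidence test uses HECSI. Clinical assessments are listed separately from HECSI at each visit, and the purpose clause in the follow-up sentence can be read as covering the photographs too. The code-break paragraph hints that the treating physician may not routinely know the allocation. A journal article may also leave the adverse event form and its grading to the full protocol.

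Much of this stands, and it rules out several stronger readings:

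- **That HECSI is the only scheduled source.** The separate clinical assessments and the photographs contradict this.
- **That objective 4 cannot be answered.** The separate adverse event data and the planned test mean that it can be, although less reliably than it should be.
- **That drug reactions contaminate the efficacy score and a checklist would cure it.** The Introduction lists erythema, vesicles and fissures as features of hand eczema, so overlap is plausible. The article does not list the HECSI items or give reaction rates, so this remains an inference. A separate checklist would in any case leave HECSI scored as before.
- **That the small sample shows the size of the defect.** With 36 per arm, two-sided Fisher tests give p = 0.054 for 5 versus 0 events and p = 0.025 for 6 versus 0. Zero events in 36 leaves a one-sided 95% upper bound of 1 − 0.05^(1/36) = 8.0%. These figures are correct, but they follow from the sample size and would be the same with perfect recording.
- **That the plan intends to infer fewer side effects from a non-significant test.** The phrase "offering a more targeted approach with fewer side effects" belongs to a conditional statement about a favourable outcome. No such inference is planned.

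What the reply does not remove is the sentence itself. It assigns side effects to a severity score, and this is something the article states, not a detail it leaves out. The missing form or grading scale is not part of the point.

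**Conclusion.** The point holds as a badly fixed measurement choice. The follow-up section gives HECSI a side-effect role that the Discussion does not support. The only other stated elicitation route depends on what participants volunteer, with no stated blinding of those who record it. Capture may therefore be incomplete or uneven between arms, which makes the answer to objective 4 and the incidence comparison less reliable without making them impossible.

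No numerical size can be attached from the documents. The conclusion assumes that the clinical assessments are not already a structured search for local reactions. If the full protocol shows that they are, only the wording needs correcting. The change is worth making before enrolment, because reactions missed at a visit cannot be recovered afterwards. The Study status section says that the trial has not started.

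**What to change.** 1. In the follow-up visits paragraph of the Interventions section, delete side effects from the purpose of HECSI, so that it is recorded for efficacy only. Bring the sentence into line with the adverse event paragraph under Enrollment and with the Statistical analysis section.
2. State that at weeks 2 and 4 the examiner completes the same fixed list of local reactions, each marked present or absent, for every patient in both arms. The list is kept separate from HECSI and adds to the adverse events that participants report. Its content is for the investigators to set.
3. In the Statistical analysis section, add the proportion of patients with at least one listed reaction in each arm and the risk difference with its 95% confidence interval, alongside the planned chi-square or Fisher's exact test.

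The cost is a short form at two visits that already take place, plus a few lines of text. A fixed list makes the search for reactions uniform. It does not mask the examiner, and it does not change how HECSI is scored.

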### Enrollment

1.
**Recruitment:** The recruitment process will commence at the Dermatology outpatient department (DVL) of AVBRH Sawangi Meghe, Wardha, from March 2023. A designated study coordinator will identify potential participants based on clinical diagnosis and eligibility criteria. Eligible patients will be provided with detailed information about the study, and the purpose, risks, and benefits will be explained.2.
**Informed consent:** Written and signed informed consent will be obtained from all eligible patients willing to participate in the study. The consent form will include information about the nature of the study, potential risks and benefits, confidentiality assurances, and the voluntary nature of participation.3.
**Screening and inclusion/exclusion criteria:** Eligible participants will undergo a screening process to confirm their clinical diagnosis and ensure they meet the inclusion criteria while excluding those who meet any exclusion criteria. The study coordinator will collect relevant medical history and conduct a thorough examination to confirm the diagnosis of hand eczema.4.
**Baseline assessments:** Baseline assessments will include the collection of demographic information, medical history, and baseline Hand Eczema Severity Index (HECSI) scores. Clinical photographs of affected areas will be taken during followup visits for documentation and comparison.5.
**Randomization and allocation:** After obtaining informed consent and confirming eligibility, participants will be assigned to either Group 1 (Clobetasol Propionate) or Group 2 (Tofacitinib) through computer-generated randomization. Age and gender cross-matching will be performed to ensure balanced groups.6.
**Assignment of interventions:** Participants will be provided with the assigned treatment (topical Clobetasol Propionate 0.05% ointment or topical Tofacitinib 2% ointment) along with detailed instructions for application.7.
**Follow-up appointments:** Participants will be scheduled for followup visits at 2 weeks and 4 weeks after the initiation of treatment. The study coordinator will communicate the importance of attending all followup appointments and the need for adherence to the assigned treatment.8.
**Monitoring adherence:** Adherence to the assigned intervention will be monitored through self-reporting, return of unused medications, and documentation during followup visits.9.
**Data collection:** Data collection will include clinical assessments, HECSI score recording, and the capture of clinical photographs during each followup visit.10.
**Adverse event reporting:** Participants will be encouraged to report any adverse events or concerns during the study. Adverse events will be documented, assessed for severity, and reported to the Institutional Ethics Committee as per regulatory requirements.11.
**End of study:** The study will conclude in September 2025, and participants will be thanked for participating. Final data analysis and interpretation will be conducted, and the study findings will be disseminated through publications and presentations.

### Sample size

Effect of topical tofacitinib for hand eczema = 81.7%

Effect of topical steroid for hand eczema = 68%

Clinically significant at (δ) = 25%

$$N={\left(1.64+0.84\right)}^{2}*\left(0.817\right)\;\left(1–0.817\right)+0.68\;\left(1-0.68\right)/{\left(0.25\right)}^{2}=36$$

Sample size = 36

Total sample size = 72 (36 per group)

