### Statistical analysis

The statistical analysis for this comparative study between topical Tofacitinib 2% ointment and topical Clobetasol Propionate 0.05% ointment in managing hand eczema will encompass a comprehensive approach utilizing appropriate parametric and non-parametric tests. The primary focus will be on the change from the baseline of the Hand Eczema Severity Index (HECSI) score. In the initial stage, descriptive statistics will be employed to summarize the baseline characteristics of participants in both treatment groups. Continuous variables will be presented as mean and standard deviation (or median and interquartile range), while categorical variables will be expressed as frequencies with percentages.

The comparative analysis will be conducted using an independent t-test or Mann-Whitney U test for the primary outcome—change from baseline in HECSI score. The choice between tests will depend on the data distribution, and statistical significance will be determined with a threshold of p<0.05. After the primary analysis, subgroup analyses may be undertaken to explore potential variations in treatment response based on age, gender, and baseline severity. Safety and adverse events will be summarized, and the incidence rates between the two treatment groups will be compared using Chi-square or Fisher’s exact test.

The handling of missing data will be addressed, potentially utilizing multiple imputations to enhance the robustness of the results. Sensitivity analyses may be performed to assess the impact of outliers or influential data points on the overall findings.

Exploratory analyses will investigate potential relationships between treatment response and additional factors, such as patient demographics or specific characteristics of hand eczema. Statistical software such as R Studio Version 4.3.1 will execute these analyses.

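### The sample size is calculated for two proportions, but the primary outcome is continuous HECSI change, so the 36 per group and its implied 80% power do not apply to the primary test

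*Protocol article*

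**What the plan says.** The Sample size section gives two planning values, "Effect of topical tofacitinib for hand eczema = 81.7" per cent and "Effect of topical steroid for hand eczema = 68" per cent, and a clinically significant difference of 25 per cent. It combines them in a formula with a p(1−p) term for each arm and the z-values 1.64 and 0.84, and arrives at 36 per group, 72 in total.

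The Methods paragraph of the Abstract says: "The primary outcome measure is the change from baseline in the Hand Eczema Severity Index (HECSI) score, assessed at two weeks and four weeks". The Statistical analysis section tests that outcome with an "independent t-test or Mann-Whitney U test for the primary outcome—change from baseline in HECSI score". A test for proportions appears in that section only for adverse events, where "the incidence rates between the two treatment groups will be compared using Chi-square or Fisher’s exact test".

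The article defines no HECSI responder and plans no responder analysis. It gives no standard deviation of HECSI change and no HECSI difference to be detected.

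**The concern.** A sample size calculation supports a trial only if it refers to the comparison that decides the trial. Here the calculation concerns a difference between two proportions, while the deciding comparison concerns the mean or rank of a score change. Nothing on the HECSI scale enters the formula, so 36 per group says nothing about the power of the t-test or Mann-Whitney test.

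Two readings of the percentages are possible, and neither closes the gap. If they are responder rates, they belong to an endpoint that the trial neither defines nor analyses. If they are mean percentage improvements, p(1−p) is the wrong variance and an SD is needed.

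What is at stake is interpretation. Both arms receive active treatment, so a modest difference between them is possible. Without a stated detectable HECSI difference, a reader of a non-significant result cannot tell what the trial could have found or ruled out.

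**Working it through.** **Inputs from the Sample size section.** p₁ = 0.817, p₂ = 0.68, δ = 0.25, z-values 1.64 (one-sided 5%) and 0.84 (80% power), 36 per group. The Statistical analysis section gives p < 0.05 without naming a side.

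**Step 1: reproduce the stated size.**
- Variance sum: 0.817 × 0.183 + 0.68 × 0.32 = 0.1495 + 0.2176 = 0.3671.
- n per group = (1.64 + 0.84)² × 0.3671 / 0.25² = 6.1504 × 0.3671 / 0.0625 = 36.13, stated as 36.

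The figure reproduces as an unpooled two-proportion calculation, with the variance sum bracketed. Every quantity in it is a proportion or a z-value.

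**Step 2: what 36 per group means for the primary test.** In the normal approximation, the detectable standardised difference is d = (z_α + z_β) × √(2/n), with √(2/36) = 0.2357.
- Two-sided 5%: (1.96 + 0.84) × 0.2357 = 0.66 SD. Exact noncentral t: 0.67 SD.
- One-sided 5%: (1.64 + 0.84) × 0.2357 = 0.58 SD. Exact noncentral t: 0.59 SD.
- Mann-Whitney, two-sided, normal data assumed (relative efficiency 0.955, so effective n = 36 × 0.955 = 34.4): 0.69 SD.

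**Step 3: power over a range of assumed differences.** The article gives no standardised difference, so the first column is an assumption. Power and n come from the exact t-test.

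| Assumed difference (SD) | Power at 36 per group, two-sided 5% | Power at 36 per group, one-sided 5% | n per group for 80%, two-sided |
|---|---|---|---|
| 0.3 | 24% | 35% | 176 |
| 0.4 | 39% | 51% | 100 |
| 0.5 | 55% | 68% | 64 |
| 0.6 | 71% | 81% | 45 |
| 0.7 | 83% | 90% | 34 |
| 0.8 | 92% | 96% | 26 |

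**Step 4: the reading as mean percentage improvement.** At two-sided 5%, 36 per group gives 80% power only if the SD of percentage improvement is at most difference / 0.6696.
- For the gap between the two planning values, 81.7 − 68 = 13.7 points: 13.7 / 0.6696 = 20.5 points.
- For the stated 25 points: 25 / 0.6696 = 37.3 points.

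No SD is given, so neither condition can be checked.

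**Step 5: is there a corrected N?** None can be computed, because it needs a HECSI SD and a target HECSI difference and the article gives neither. What can be stated is the detectable difference at the planned N.

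**The case against.** The strongest reply is that no shortage of patients has been shown, and this stands. The 0.3 SD and 0.5 SD rows above are illustrations, not effects that the article predicts. Suppose the percentages are responders above a cut-off on a normally distributed score with equal SDs. A 25-point difference then corresponds to about 0.64 SD (68% against 43%), 0.74 SD (81.7% against 56.7%) or 1.0 SD (93% against 68%). Two-sided t-test power at 36 per group would be about 77%, 87% and 99%. On that assumption, the change of endpoint need not leave the trial short of power. For the 13.7-point gap the same conversion gives 0.44 SD and 45%, but that turns on whether 25 points is the right δ, which is a separate question.

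The side of alpha also matters. The formula uses a one-sided value and the analysis section names no side, so quoting only two-sided results would fold a second issue into this one. Both are therefore shown.

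Three stronger readings are tempting, and the document does not support them:
- **72 is too few.** It would be enough if the true difference is about 0.67 SD or more (two-sided), and nothing in the article says whether it is.
- **The 81.7 per cent contradicts the Discussion**, which says of tofacitinib that "its efficacy and safety in hand eczema remain to be elucidated". A planning value can rest on limited data while efficacy is still unsettled, and the article does not show where the value came from. No contradiction is established.
- **Dropout makes the size inadequate.** The article gives no loss rate, treatment lasts four weeks, and multiple imputation is mentioned as a possibility. Any loss figure is an assumption.

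None of this connects the proportion formula to the HECSI comparison. An unseen analysis plan would not connect them either, because the article states both the calculation and the primary test, and they refer to different quantities.

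**Conclusion.** The point holds as a mismatch between the calculation and the primary analysis. The 36 per group reproduces (36.13), but only for a comparison of two proportions that the trial does not plan to make on any efficacy outcome. The implied 80% power does not carry over to the t-test or Mann-Whitney test on HECSI change.

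With 36 evaluable per group, 80% power applies to a difference of about 0.67 SD (t-test, two-sided 5%), 0.59 SD (t-test, one-sided 5%) or 0.69 SD (Mann-Whitney, two-sided). These figures assume equal SDs, normally distributed changes and a single comparison at one visit. The conclusion about the mismatch depends on none of those assumptions. Whether 72 patients are enough remains open until a HECSI SD and a relevant HECSI difference are stated.

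**What to change.** Replace the proportion calculation with a statement for the primary HECSI comparison at the planned size, for example: *36 evaluable patients per group give 80% power to detect a difference in HECSI change of about 0.67 SD with a t-test at two-sided 5% (about 0.69 SD with Mann-Whitney if the data are normal).* If a one-sided 5% test is intended, say so and give 0.59 SD for the t-test.

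Then:
- Express the difference in HECSI points, using an SD that is sourced or labelled as assumed. For illustration only, assumed SDs of 10, 20 and 30 points give 0.67 × SD = 6.7, 13.4 and 20.1 points.
- Say which visit the statement refers to. The Abstract names two weeks and four weeks without choosing.
- Remove the 81.7 and 68 per cent inputs, or attach them to a defined secondary responder endpoint.
- Show loss to follow-up, if at all, as a labelled assumption. For example, 31 evaluable per group (an assumed loss of about 14%, since 5/36 = 0.14) moves the two-sided detectable difference to 0.72 SD.

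The direct cost is protocol wording, and the Study status section says that the trial has not started. The downside is that the detectable effect becomes explicit and fairly large. If it looks implausible in HECSI points, the number of patients has to be reconsidered.

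### The sample size divides by δ = 25% although its own two rates differ by 13.7 points; read as proportions, 36 per group has about 27% two-sided power for those rates, not the 80% implied

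*Protocol article*

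**What the plan says.** The Sample size section of the protocol article gives three planning figures: "Effect of topical tofacitinib for hand eczema = 81.7" per cent, "Effect of topical steroid for hand eczema = 68" per cent and "Clinically significant at (δ) = 25" per cent. It puts the first two into a variance term and the third, squared, into the denominator, with multipliers 1.64 and 0.84. The result is "Total sample size = 72 (36 per group"). Power is not given in words; 0.84 is the normal quantile for 80%.

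The Statistical analysis section plans an "independent t-test or Mann-Whitney U test for the primary outcome—change from baseline in HECSI score", and says that "statistical significance will be determined with a threshold of p<0.05", without naming one or two sides. The third item under Objectives is to compare the two ointments. No non-inferiority or equivalence aim or margin appears anywhere in the article.

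**The concern.** In this two-proportion formula, the denominator is the difference to be detected and the variance is evaluated at the two rates assumed under the alternative. One pair of rates should supply both. Here the rates are 13.7 points apart and the denominator is 25 points, so they do not describe the same alternative. With 68% on steroid, a 25-point gain would put tofacitinib at 93%, not 81.7%.

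This section is the only justification given for 72 patients. A reader will take from it that the trial has 80% power for the effects listed. If it does not, a non-significant comparison with an active control could be misread as showing that the two ointments are alike.

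**Working it through.** **Inputs** (Sample size section): p1 = 0.817, p2 = 0.68, δ = 0.25, z values 1.64 (one-sided 5%) and 0.84 (80% power), 36 per group. The value 1.96 is used where the test is taken as two-sided at 5%, because the analysis section does not fix the sides.

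**1. Reproduce the plan's figure.**

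Variance sum: V = 0.817 × 0.183 + 0.68 × 0.32 = 0.3671.

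n = (1.64 + 0.84)² × V / δ² = 6.1504 × 0.3671 / 0.0625 = 36.1.

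This matches the plan's 36. The printed formula has no brackets around the variance sum and, read literally, gives 4.4, so the bracketed form was evidently used.

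**2. Put the plan's own difference in the denominator.** 0.817 − 0.68 = 0.137, and 0.137² = 0.018769.

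- z = 1.64: 6.1504 × 0.3671 / 0.018769 = 120.3, so 121 per group.
- z = 1.96: 2.80² × 0.3671 / 0.018769 = 153.3, so 154 per group.

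**3. Power at 36 per group for 81.7% vs 68%.** Standard error = √(0.3671 / 36) = 0.1010, and 0.137 / 0.1010 = 1.357.

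- z = 1.64: Φ(1.357 − 1.64) = Φ(−0.283) = 38.8%.
- z = 1.96: Φ(1.357 − 1.96) = Φ(−0.603) = 27.3%.

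Exact enumeration of the z/chi-square test gives 37.5% one-sided and 26.5% two-sided, so the normal approximation is not driving the result.

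**4. Power at 36 per group for a 25-point difference.**

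| Scenario | Power |
|---|---|
| Plan's variance, one-sided | about 80% |
| Plan's variance, two-sided | Φ(0.25 / 0.1010 − 1.96) = about 70% |
| 93% vs 68% with its own variance, two-sided | 80.5% (exact chi-square 80.2%) |

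For the last row, the variance sum is 0.93 × 0.07 + 0.68 × 0.32 = 0.2827, the standard error is √(0.2827 / 36) = 0.0886, and Φ(0.25 / 0.0886 − 1.96) = Φ(0.861) = 80.5%.

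With δ = 0.25 and the plan's variance, a two-sided test would need 2.80² × 0.3671 / 0.0625 = 46.05, so 47 per group.

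**The case against.** The best defence is that δ is labelled as the clinically significant difference. It can be read as a minimal important difference, with the two rates serving only to estimate the variance. On that reading the arithmetic is sound: the formula returns 36 and one-sided power for 25 points is about 80%. The plan never claims in words 80% power for 13.7 points. It stands that this is an unreconciled input and not a slip in calculation. The defence does not remove the problem, because the rates printed beside δ contradict a 25-point alternative, and two-sided power for 25 points at the plan's variance is only about 70%.

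Reading δ as a non-inferiority margin with no true difference gives the same 36.1. However, the article states no such aim, and its rates are not equal. With a true 13.7-point advantage the distance to the margin would be 0.387, and n = 6.1504 × 0.3671 / 0.387² = about 15, so 36 does not follow from those rates either.

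Two further objections limit what can be said:

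- **The planned test is a different one.** A reader might infer that the trial is more likely than not to be non-significant on its primary test. The article does not support that. The primary outcome is change in HECSI, and no SD or mean difference is given for it.
- **The article speaks of an effect and defines no responder.** The p(1 − p) terms treat the figures as proportions. If they were mean percentage improvements, two-sided t-test power for 13.7 points at 36 per group would be about 82%, 63%, 48% or 30% for an assumed SD of 20, 25, 30 or 40 points. These SDs are assumptions, since the article gives none.

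A reader might also compute 2.80 × 0.1010 = 28 points as the two-sided detectable difference. That holds the variance at 81.7% vs 68%. From a 68% control rate, 25 points already gives 80.5% power and 28 points (96% vs 68%) about 91%. The 28-point figure should therefore not enter the protocol.

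**Conclusion.** The point holds for the sample size calculation as written. Its rates and its δ describe different alternatives, and no margin-based hypothesis explains the gap. Taking the figures as proportions, 72 patients give about 27% two-sided power (39% with z = 1.64) for 81.7% vs 68%, against the 80% implied by 0.84. The formula would need about 121 or 154 per group for that difference.

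The conclusion rests on the proportion reading, which is the one the formula itself uses. It does not extend to the HECSI-change test, whose power is unknown from this document. The stated basis for 72 patients should be corrected before the trial relies on it; the Study status section says that the trial has not started.

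**What to change.** Rewrite the Sample size section without adding patients:

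1. Reconcile δ with the stated rates: say what 25 points represents and why it differs from 13.7.
2. State that 36 per group gives about 27% two-sided power for 81.7% vs 68%. State that about 80% is reached only for a difference of about 25 points, either one-sided with the plan's variance or two-sided for 93% vs 68%. The 93% is only 68% plus 25 points, shown for illustration. It appears nowhere in the article and should not replace 81.7% as the planning rate.
3. State that the calculation concerns a comparison of proportions and that power for the HECSI-change primary test cannot be derived from it.
4. State that a non-significant result will be reported as inconclusive, with its 95% CI.

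The cost is a paragraph of text and a less favourable power statement.
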